## Abstract

**Background:**

Telegerontology is an approach using videoconferencing to connect an interdisciplinary team in a regional specialty center to patients in rural communities, which is becoming increasingly practical for addressing current limitations in rural community-based dementia care.

**Objective:**

Using the remotely-delivered expertise of the Telegerontology dementia care team, we aim to enhance the caregiver/patient/physician triad and thereby provide the necessary support for the person with dementia to “age in place.”

**Methods:**

This is a cluster randomized feasibility trial with four rural regions in the province of Newfoundland and Labrador, Canada (2 regions randomly assigned to “intervention” and 2 to “control”). The study population includes 22 “dementia triads” that consist of a community-dwelling older Canadian with moderate to late dementia, their family caregivers, and their Primary Care Physician (PCP). Over the 6-month active study period, all participants will be provided an iPad. The intervention is intended as an adjunct to existing PCP care, consisting of weekly Skype-based videoconferencing calls with the Telegerontology physician, and other team members as needed (occupational therapist, physical therapist etc). Control participants receive usual community-based dementia care with their PCP. A baseline (pre-) assessment will be performed during a home visit with the study team. Post intervention, 6- and 12-month follow-up assessments will be collected remotely using specialized dementia monitoring applications and Skype calls. Primary outcomes include admission to long-term care, falls, emergency room visits, hospital stays, and caregiver burden.

**Results:**

Results will be available in March of 2018.

**Conclusions:**

Results from this study will demonstrate a novel approach to dementia care that has the potential to impact both rural PCPs, family caregivers, and people with dementia, as well as provide evidence for the utility of Telegerontology in models of eHealth-based care.

## Introduction

In 2011 the estimated prevalence of dementia in Canada was 340,000 with just under one-third (109,500) living at home [1]. Community-based dementia care relies heavily on family caregivers, with 92% of surveyed Canadians with dementia reporting friends or family members managing care and transportation. A further 58%-92% report family caregivers assisting with personal care, medical care, activities of daily living, meal preparation, and emotional support [1]. With such high demands on family caregivers of people with dementia, they are at increased risk of stress and burden [2], medical and psychiatric comorbidities [3,4], and social isolation [5]. Rates of dementia [6] and mortality [7] are also higher among caregivers, perpetuating and compounding the issue into a cycle of caregiving that leads to early disability, cognitive decline, and death. These detrimental effects of caregiving can also translate to negative consequences for people with dementia, including earlier institutionalization [8] and increased mortality [9]. Approaches that support the caregiver as well as the patient are therefore fundamental to community-based dementia care.

The health care triad model of dementia care proposes management of dementia that is both family and patient centered, while acknowledging that the primary care physicians (PCPs) are usually the first contact in the health care system for persons with dementia and their family caregivers [10]. This integrative approach values symptom diagnosis and management, medication management, and emotional support with a focus on comprehensive care coordination [10] and has been employed in both rural and urban settings [11]. And while this is a favorable approach, PCPs in rural Canada can face challenges when attempting to provide adequate community-based care for dementia patients and their families. Although rural Canadian PCPs are more accessible than specialist services, some research suggest that they may have limited training in dementia specific management [12]. Rural PCPs also report a need for better collaboration, partnerships, and integration of services [13] in order to provide the very best care for people with dementia and their families. How best to support the dementia triad in rural areas of Canada is still poorly understood, and few studies have explored the utility of the health care triad model of dementia care as a theoretical basis for an intervention [11]. Taken together, this evidence demonstrates a clear need to design and deliver evidence-based services to support people living with dementia in the community, their family caregivers, and PCPs [14].

Technology-based intervention is one line of inquiry aiming to address support for rural dementia care triads. There is some evidence to suggest that people with dementia and their family caregivers are already using the Internet to access Internet-based health resources [15]. Internet interventions for family caregivers of people with dementia have shown promise addressing caregiver well-being [16-18]. Less is known about how the Internet can be used to manage dementia at home. Some research suggests that videoconferencing is a valid method to assess dementia [19,20]. Telemedicine has been used to accurately diagnose dementia [21] and telehealth has effectively supported pre-assessment and follow-up when used in combination with an in-person interdisciplinary memory clinic assessment [22].

This paper describes a novel approach to rural community-based dementia care that combines the health care triad model of dementia care (patient, caregiver, and PCP) with an innovative Telegerontology intervention. Telegerontology is an approach using videoconferencing to connect an interdisciplinary team in a regional specialty center to people in rural communities. The aim of this study is to use Telegerontology in order to systematically detect and address care needs of people with dementia and their family caregivers, while augmenting PCP relationships with dementia patients and their families. The overall objective is to assist people with dementia to age successfully “in place.” Furthermore, findings from this study will be used to identify feasibility issues that will inform the design of a full-scale randomized control trial (RCT).

## Methods

### Aim

Using the remotely delivered expertise of the Telegerontology dementia care team, we aim to enhance the caregiver/patient/physician triad and thereby improve rural community-based care for people with dementia.

### Objectives

The objectives will be as follows:

Test Telegerontology’s ability to enhance the caregiver/patient/ PCP triad and thereby improve care “in place” (ie, health care utilization) for people with dementia.Assess and optimize a remote monitoring method for managing care of people with moderate- to late-stage dementia living at home in rural Canada in order to inform the design of a full-scale RCT.Explore issues related to care of people with dementia from the caregivers’ and PCPs’ perspectives.

### Study Design

#### Overview

The study was approved by the local research ethics authority. This is a cluster randomized feasibility trial assessing 4 rural regions (2 per study arm) comparing usual rural community-based dementia care to Telegerontology plus usual rural community-based dementia care. Using the opaque envelope method, the rural regions will be randomized to control or intervention after baseline assessment. The intervention will last 6 months with the measurement of outcomes taking place at baseline, after 6 months (post), with follow-up occurring 6 months (6-month follow-up) and 12 months (12-month follow-up) after cessation of the intervention.

The study population will include 22 “dementia triads” that consist of a community-dwelling older Canadian with moderate to late dementia, their family caregivers, and their PCP. The study will be carried out in communities located in rural areas of Newfoundland and Labrador, Canada but will be monitored remotely from the metropolitan city of St John’s, Newfoundland and Labrador. We define *rural* in this study to mean a community with less than 10,000 residents and a location that is greater than two hours’ drive from the metropolitan city, where specialist health services are located. Before randomization, recruitment will begin by enrolling PCPs from rural communities who will make initial contact with potential participants. Written informed consent will be obtained for every individual agreeing to participate in the study except in the case for an individual with advanced dementia who lacks capacity, in which case consent will be obtained from the substitute decision maker. Consent will be reviewed without the presence of the PCP in order to limit undue influence for participation in the study.

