**Figure 1 figure1:**
[figure not shown]
Study flow. After PCP recruitment, participant referrals and home assessment, the rural regions will be randomized to control or intervention.

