### Sample Size Calculation

Sample size was calculated based on regional population statistics rather than for statistical power, targeting 2.5% of the population of community-dwelling dementia patients in the target region. Based on prevalence estimates, 98.5/1000 Canadians over 40 years of age have dementia with 34% living at home. The total population for the entire recruitment region of the present study is approximately 38,490 suggesting that the total population of community-dwelling dementia patents is approximately 1,289. Therefore, we aim to recruit 42 participants for inclusion in this study accounting for a 30% dropout rate.

**Table 2 table2:** Occupational Therapy Home Safety Video checklist.

Video	Description
1	A short video walking from the driveway outside, going into the house through the usual entry door, straight through the kitchen/living area into the person's bedroom and then into the bathroom.
2	Kitchen (short video)
3	Bedroom (short video)
4	Bathroom (short video)
5	Living room (short video)
6	Stairs (short video)
7	Laundry (short video)

Qualitative interview questions.PCP Interview QuestionsDescribe the care required to manage people with dementia in their homes.From your point of view, how well are your patients being managed at home?How would you envision an ideal circle of care to maintain people with dementia in their homes?Caregivers Interview QuestionsFrom your point of view, how well are you managing the health of your loved one at home?In an ideal world, how could things be improved? What are the main challenges you experience? Have you had successes caring for your loved one?

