### Study Strengths and Limitations

The proposed study has several notable methodological strengths. The initial home visit is designed to help build rapport between the Telegerontology physician and participants. This method is also in keeping with previous research, which suggests that telehealth has effectively supported assessment and follow-up when used in combination with an in-person interdisciplinary memory clinic assessment [12].

Next, the Telegerontology measurement framework, based on the ICF and Wilson-Cleary models provides in-depth, multi-factor profiles of participants contributing to a methodology that acknowledges the broad range of factors that can impact health planning and management of community dwelling people with dementia. Likewise, the inclusion of caregivers and PCPs as participants adds further depth to both characterizing and assessing participants with dementia by acknowledging and building on the role of the caregiver and PCP in the health care triad. The development of remote monitoring apps from existing validated scales to assess dementia and caregiver burden is also a methodological strength of this study.

There are also several limitations in the protocol. The relatively small sample size can be seen as a drawback, however, based on regional prevalence estimates, the sample size is realistic for the target population. There may also be considerable variability between participants within a group, further complicating statistical analysis. Next, the Telegerontology physician serves as both an interventionist and assessor. This has the potential to create bias, however the primary outcome measures were selected partially to address this issue since they are based on participant self-report/chart review rather than clinical assessment.

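### Four regions are drawn 2 v 2 by envelope after baseline assessment with no balance constraint described, so the worst balanced of the three possible splits has a 1 in 3 chance although it could be excluded cheaply

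*Protocol article*

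**What the plan says.** The Overview under Study Design fixes four rural regions, two per arm, and gives the method and timing of allocation: "Using the opaque envelope method, the rural regions will be randomized to control or intervention after baseline assessment". The legend to Figure 1 confirms the order: "After PCP recruitment, participant referrals and home assessment, the rural regions will be randomized to control or intervention". No stratification, matching, minimisation or other restriction is described.

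Table 1 ticks the Caregiving Hassles Scale (a primary outcome) and the Global Deterioration Scale at baseline. Both are therefore available for every region before the draw, as is the number of triads recruited in each region.

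Statistical Analysis compares the arms by repeated measures ANOVA or by an independent t test, and names no adjustment for baseline or region.

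**The concern.** Randomising after baseline assessment lets the trialists use what they have measured to avoid a poor allocation. As described, the draw makes no such use of it.

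With two regions per arm, one unusual region is enough to tilt an arm on dementia severity, caregiver burden or number of triads. A t test on post-intervention values carries that tilt into the estimated arm difference. Four clusters leave very little information for correcting it later. The event outcomes (emergency room visits, hospital stays, falls, long-term care admission) have no baseline tick in Table 1. If the table is right, they cannot be adjusted for their own baseline values, and balance on severity at allocation is the main protection available.

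**Working it through.** **Inputs from the article.** Four regions, two per arm (Overview). Two sample sizes: 22 triads (Abstract and Overview), or 22/4 = 5.5 per region; and "we aim to recruit 42 participants for inclusion in this study accounting for a 30% dropout rate" (Sample Size Calculation), or 42/4 = 10.5 per region. The 42 reproduces: 38,490 × 0.0985 × 0.34 = 1,289; 2.5% of that is 32.2; 32.2 × 1.3 = 41.9. The article does not reconcile 22 with 42, so both are carried below. It gives no figure on baseline balance.

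**Assumptions.** ICC 0.05, range 0 to 0.20; the article gives none. Region means are normal, regions equal in size, and baseline variables independent. A difference above 0.5 SD counts as a bad imbalance.

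**Step 1: allocations.** C(4,2) = 6 labelled allocations. Each split appears under two labellings, so there are 6/2 = 3 splits, each with probability 1/3.

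**Step 2: unrestricted draw.** In individual-SD units a region mean has variance v = ICC + (1 − ICC)/m. The difference between two arms of two regions has variance v/2 + v/2 = v.
- 22 triads: v = 0.05 + 0.95/5.5 = 0.223, SD 0.472. Mean absolute difference = 0.472 × √(2/π) = 0.38 SD. P(>0.5 SD) = 2[1 − Φ(0.5/0.472)] = 29%.
- 42 participants: v = 0.05 + 0.95/10.5 = 0.140, SD 0.375. P(>0.5 SD) = 18%.
- Over ICC 0 to 0.20: 24% to 40% with 22; 11% to 34% with 42.

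**Step 3: restricting on one variable.** The three split contrasts are orthogonal, hence independent under normality. The best split exceeds 0.5 SD only if all three do.
- Best split, 22 triads: 0.289³ = 2.4% (1.4% to 6.2% over the ICC range).
- Best split, 42 participants: 0.182³ = 0.6%.
- Dropping only the worst split, 22 triads: [3p − (1 − (1 − p)³)]/2 with p = 0.289 gives (0.867 − 0.641)/2 = 11%.

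**Step 4: several variables.** Simulation, choosing the split with the smallest sum of squared differences (22 triads, ICC 0.05):

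| Variables balanced | Mean imbalance per variable | Chance above 0.5 SD on a given variable |
|---|---|---|
| None (unrestricted) | 0.38 SD | 29% |
| One | 0.16 SD | 2% |
| Two | 0.22 SD | 7% |
| Three | 0.25 SD | 10% |

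The chance that at least one of three variables exceeds 0.5 SD falls from 64% to 28%. For at least one of five it falls only from 82% to 57%, so the list of factors has to be short.

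**Step 5: what is given up.** The smallest two-sided randomisation-test P is 2/6 = 0.33 with six allocations, 2/4 = 0.50 if the worst split is dropped, and 2/2 = 1.00 if only the best is kept.

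**The case against.** The strongest reply is that the opaque envelope describes concealment and does not say that the draw is unrestricted; a balance rule could stand in a full protocol that is not shown. That is a fair limit. The point is confined to the method as described, and if a restriction exists, stating it settles the matter.

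Four stronger readings are tempting, and the article does not support them.
- A reader might infer that every baseline value is known at the draw. Outcome Measures says that primary and secondary outcomes are collected at baseline, but Table 1 ticks only the Caregiving Hassles Scale among them, leaving four of the five primary outcomes without a baseline value. The two places need reconciling.
- A reader might infer that balance is free. It is not, as Step 5 shows. The practical loss is small: six allocations already cannot give P below 1/3, and Statistical Analysis does not expect significance.
- A reader might take the fall from 29% to 2% as the general gain. It applies to one variable only, and the best of three splits may still be poor.
- A reader might cite the limitation "There may also be considerable variability between participants within a group, further complicating statistical analysis" in support. It concerns spread within a group and says nothing about imbalance between regions or arms.

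It is also true that imbalance need not reach every comparison. A group-by-time term in the repeated measures option would take account of a starting difference in Caregiving Hassles; the t test option would not. Finally, this is a feasibility trial, and balancing measured covariates leaves region and treatment confounded with two regions per arm. That limits how much is at stake but does not remove the advantage of restricting the draw.

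**Conclusion.** The concern holds in a limited form. The described method leaves a 1 in 3 chance of the worst of three splits although suitable balancing information is in hand. That 1 in 3 follows from the design alone and needs no assumption, but worst is relative: all three splits may be acceptable, or none.

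The sizes in SD units rest on the assumed ICC, equal regions, normal and independent variables, and the 0.5 SD threshold. Over ICC 0 to 0.20 the gain on one variable remains large at either sample size; with two or three variables it is clear but more modest. This is an inexpensive improvement to the design. It is not an error that invalidates the trial, and it would not make arm differences from four regions firm evidence of effect.

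**What to change.** Replace the allocation sentence with restricted randomisation:

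1. Before baseline data are seen, name at most two or three region-level balance factors: number of triads, mean baseline Caregiving Hassles score, mean Global Deterioration Scale stage. Fix the imbalance score in advance.
2. After the last baseline visit, someone outside the study team lists the three splits and scores them.
3. Keep the best balanced split, or at least drop the worst, and randomise among the remaining allocations with concealment kept. Each region still has a 50% chance of either arm.
4. If an unrestricted draw is preferred, give the reason.

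The cost is one paragraph of text, a short task for an independent person, and the reduction from six allocations to two (or four). Keeping only the best split also means that the same two regions always go together and only the label is random.

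The Results section says that data collection ended in April 2017, so this trial's draw cannot be changed. What remains is to state whether any restriction was used, show baseline characteristics by region as well as by arm, take account of baseline Caregiving Hassles when comparing that outcome, and interpret arm differences cautiously. The allocation method can still be set for the full-scale trial that this study is meant to inform.

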#### Inclusion Criteria

##### Dementia Patient/Caregiver Dyad

Community-dwelling adults aged ≥60 years will be screened by PCP for having a score of 4 or greater on the Global Deterioration Scale [23], and have a formal diagnosis of dementia based on the Diagnostic and Statistical Manual of Mental Disorders IV. Caregiver is defined as an individual who self-identifies as providing support with instrumental activities of daily living in an informal (friend or family) capacity and who was referred to the study by the PCP.

##### PCPs

PCPs located in a rural area of Newfoundland and Labrador must be willing to participate in a 1 hour focus group, and must refer at least 1 community-dwelling patient with moderate/late-stage dementia who agrees to participate in the study.

#### Exclusion Criteria

##### Dementia Patient/Caregiver Dyad

Patients with a diagnosed comorbid psychiatric condition (eg, schizophrenia, bipolar disorder, psychoses not yet determined) will be excluded. In addition, those who are currently participating in other studies or experimental therapies will be excluded.

##### Dropout

Dropout is defined as any participant who voluntarily withdraws or who cannot be successfully contacted within a month of the defined follow-up times. The impact of dropouts on statistical analysis, including intention to treat, will be discussed subsequently.

#### Control and Intervention Group

Over the 6-month active study period, all participants will continue usual community-based dementia care with their PCPs. All participants will also be given new iPads by the study team with Skype and the specialized dementia monitoring applications installed. In addition, all participants will be referred to the Canadian Alzheimer Society’s FirstLink Program [24,25] which includes a 10-week education session for caregivers that can be accessed remotely by Skype, and provided links to Internet-based health resources for dementia caregivers. Because FirstLink is already available in the target communities, all participants were referred in order to standardize exposure across groups.

PCPs of all participants will also receive a written report of the initial home assessment at the beginning of the 6-month active study period to implement at their discretion. Study flow is described in detail in Figure 1.

#### Intervention Group

The intervention works as an adjunct to existing PCP care and consists of scheduled weekly Skype-based videoconferencing calls (additional calls available as needed) with the Telegerontology physician, who is a family practice geriatrician. The program’s development was based on principals of the health care triad model of dementia care [10]. Calls will focus on symptom diagnosis and management, medication management, comprehensive care coordination, and emotional support. During the 6-month intervention, the Telegerontology physician will liaise via telephone and email correspondence with the PCP and specialized geriatric team as required. The team will include a geriatrician, geriatric psychiatrist, nurse, physiotherapist and occupational therapist. Access to other allied health professionals (social worker, speech language pathologist, and recreational therapist) will also be available when deemed necessary. During this time, participant families will also have access to specialized dementia monitoring iPad applications that may be used by the Telegerontology physician in clinical decision making. Any potential changes to patient’s treatment plans will be managed by the participant’s PCP in consultation with the Telegerontology physician and acting in collaboration with the specialist gerontology health care team.

